**Fig. 3 Fig3:**
[figure not shown]
Example of training stimuli of the alcohol and cannabis version

### Baseline, post measurement and follow-ups

#### Attentional bias assessment

Attentional bias to substance-related cues is measured using the *Odd One Out Search Task* approach (originally introduced by [44]], and later modified by other researchers). In this task, participants have to identify whether 20 pictures (500 × 500 pixel), presented in a 4 × 5 matrix, all belong to the same single category or whether one picture belongs to a category distinct from all the others. Dependent on the diagnosis of the participant, all pictures belong to one of the following three categories: alcoholic drinks, non-alcoholic drinks, and flowerpots or cannabis-related objects, neutral daily life devices, and flowers, respectively for AUD and CUD. Due to these three categories, there are three conditions in which no *odd one out* picture can be found in the matrix (e.g., all 20 pictures show alcoholic drinks). Accordingly, there are six possible combinations in which an *odd one out* picture is present (e.g., 19 pictures contain cannabis-related objects and one picture shows a flower). For an overview of all nine conditions per diagnoses see Table 1. The possible combinations of conditions are balanced and the order of trials is random. The task is divided into three blocks of 24 trials each, and within each block, there will be 18 trials with an *odd one out* picture and 6 trials without an *odd one out* picture. The duration of each trial is dependent on the reaction time of the participant, but last 10 s at most. Responses are given by the answer buttons on the keyboard; 1 for ‘yes, there is an *odd one out*’ and 0 for ‘no, there is no *odd one out*’. Between trials, participants are instructed to focus their attention on a red fixation cross in the middle of the screen, which is presented for 500 ms. For both versions (alcohol and cannabis), we will use a total of 90 pictures, meaning that there are 30 different pictures per category. Per trial, the 20 pictures that are presented in the matrix are randomly drawn from the available pictures. The pictures of the alcoholic and non-alcoholic drinks [43] and the pictures of cannabis-related objects and neutral daily life devices [45–48] were used in earlier studies and permission was asked. The pictures of flowerpots and flowers were taken for the purpose of the current study.

**Table 1 Tab1:** Type and amount of trials in the Odd one out task, separated for AUD and CUD

Condition	Type of trials AUD	Type of trials CUD	Trials per block
1	20 alcohol images	20 cannabis-related images	2
2	20 soft drink images	20 neutral images other than flowers	2
3	20 flowerpot images	20 flower images	2
4	19 alcohol 1 soft drink	19 cannabis-related 1 neutral	3
5	19 alcohol 1 flowerpot	19 cannabis-related 1 flower	3
6	19 soft drink 1 alcohol	19 neutral 1 cannabis-related	3
7	19 flowerpot 1 alcohol	19 flower 1 cannabis-related	3
8	19 soft drink 1 flowerpot	19 neutral 1 flower	3
9	19 flowerpot 1 soft drink	19 flower 1 neutral	3

*AUD* = alcohol use disorder, *CUD* cannabis use disorder

Attentional bias scores will be calculated by subtracting the mean reaction time of trials with one neutral picture among 19 substance-relevant pictures (condition 4 and 5; see Table 1) from the mean reaction time of trials with one substance-relevant picture among 19 neutral pictures (condition 6 and 7). A positive score indicates that participants are faster in finding substance-relevant information within neutral information, than finding a neutral stimulus in an array of substance-relevant pictures, and thus reflect an attentional bias for substance-related cues.

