### Trial objective and hypothesis

The current study will investigate the effectiveness of a newly developed internet-based ABM (iABM) training as an add-on intervention to treatment as usual (TAU; consisting of protocolled CBT-based interventions), in alcohol and cannabis dependent outpatients. More specifically, the study will evaluate whether this new iABM training enhances treatment outcomes, and may be a cost-effective component that should be added to treatment in addiction care. The focus of the study is to examine the additional effects of iABM training on changes in substance use, craving, and relapse rates. Measurements of attentional bias will serve as a manipulation check for the efficacy of the current training to successfully modify attentional bias. This is important because only if the current iABM intervention is effective in modifying patients’ attentional bias it can be expected to have an impact on their substance use.

Based on this objective, we will test the hypothesis that patients who receive iABM intervention, compared to controls, will show less substance use, less craving, and lower relapse rates at post-measurement and 6 and 12 months after treatment. In addition, we will test if patients who received iABM intervention will show increased health and reduced physical and psychological complaints. Furthermore, we predict that these patients will show a reduction in health care usage 6 and 12 months after the intervention. Moreover, we predict that the effects on the individual and societal level will cause a decrease in societal costs that outweighs the additional costs of iABM intervention. Finally, we hypothesize that participants who show a stronger attentional bias and higher rates of craving before starting the ABM training will benefit most from this intervention.

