To test the effect of the BITT on participants’ ability to engage attention with substance-irrelevant cues while ignoring substance-relevant cues, we will test the increase in tracking time of the substance-irrelevant cue over the course of treatment. To test the effect of the BITT on participants’ ability to disengage attention from the currently attended locus whenever substance-relevant cues appear there, we will examine the change in switching time over the course of treatment. To measure transfer of the improvement in BITT performance in terms of enhanced orientation towards substance-irrelevant cues and enhanced ability to disengage from substance cues, we also included a visual search task to measure attentional bias (see below).

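### The attentional bias formula and the stated meaning of a positive score contradict each other, so the direction of the manipulation check is not fixed

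*Protocol article*

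**What the plan says.** The protocol article, under *Attentional bias assessment*, builds the score from two sets of odd-one-out trials. It is obtained by "subtracting the mean reaction time of trials with one neutral picture among 19 substance-relevant pictures (condition 4 and 5; see Table 1") and the second half of the rule reads "from the mean reaction time of trials with one substance-relevant picture among 19 neutral pictures (condition 6 and 7"). The next sentence interprets the result: "A positive score indicates that participants are faster in finding substance-relevant information within neutral information", as compared with the opposite search, "and thus reflect an attentional bias for substance-related cues".

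The score has two uses. *Trial objective and hypothesis* states: "Measurements of attentional bias will serve as a manipulation check for the efficacy of the current training to successfully modify attentional bias". *Primary and secondary outcome measures* repeats that role, and *Clinical analysis* makes the score the dependent variable of a 4 × 2 repeated measures ANOVA, the first analysis listed. *Trial objective and hypothesis* also predicts that "participants who show a stronger attentional bias and higher rates of craving before starting the ABM training will benefit most from this intervention".

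**The concern.** The scoring rule and its interpretation point in opposite directions, and nothing else in the article says which governs.

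The direction of this score matters for reading the whole trial. *Trial objective and hypothesis* says that an effect on substance use can be expected only if the training changes attentional bias. Whether bias fell, stayed level or rose therefore decides how a positive or a null clinical result is explained. The same score is the natural measure of baseline bias for the prediction about who benefits most.

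A significance test would not expose the mistake, because it is equally significant with either sign.

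**Working it through.** **Inputs, all from *Attentional bias assessment* and Table 1**

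- Term taken away: mean RT of conditions 4 and 5, one neutral target among 19 substance pictures. Call it RT(4,5).
- Term it is taken from: mean RT of conditions 6 and 7, one substance target among 19 neutral pictures. Call it RT(6,7).
- Stated meaning of a positive score: the substance target is found faster, that is, RT(6,7) < RT(4,5).

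**Step 1: the formula as written.** Subtracting A from B gives B − A, so

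score = RT(6,7) − RT(4,5).

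**Step 2: try to reproduce the stated sign.** If RT(6,7) < RT(4,5), then RT(6,7) − RT(4,5) < 0. The score is negative, whereas the article says positive. The stated sign is not reproduced.

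**Step 3: illustrative values.** The article gives no reaction times, so these are assumed. The sign does not depend on the values chosen.

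| Participant | RT(6,7), ms | RT(4,5), ms | As written: RT(6,7) − RT(4,5) | Order swapped: RT(4,5) − RT(6,7) |
|---|---|---|---|---|
| Biased towards substance cues | 2500 | 3000 | −500 | +500 |
| No bias | 2750 | 2750 | 0 | 0 |
| Opposite pattern | 3000 | 2500 | +500 | −500 |

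Only the swapped order agrees with the interpretation.

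**Step 4: consequence for the manipulation check.** Suppose a patient moves from the first row at baseline to the second row after training. Bias has fallen by 500 ms. The written score moves from −500 to 0, a change of 0 − (−500) = +500 ms. Under the stated interpretation, that is a rise in bias.

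**Step 5: consequence for baseline bias.** Ranked by the written score, the third row (+500) comes highest and the first row (−500) lowest. Read as stated, the patient with the least bias is labelled the most biased.

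**Step 6: consequence for the tests.** Multiplying the dependent variable by −1 leaves every sum of squares unchanged, so F and p are unchanged. A simulated two-group comparison (64 per group, assumed means 300 and 400 ms, SD 200 ms) gave t = −3.297 for the scores and t = +3.297 for the same scores with the sign flipped, with p = 0.00127 both times.

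**Step 7: other readings tried.**

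- *Table labels swapped against the prose.* They are not. Table 1 lists condition 6, for example, as "19 soft drink 1 alcohol", which matches the text.
- *A speed or accuracy measure, for which larger means better.* The text specifies mean reaction time.
- *Reading the subtraction the other way round.* This would give the stated sign, but it is not what the words mean.

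**The case against.** The strongest reply is that the sentence after the formula sets out the intended construct in full: faster detection of substance pictures is positive and means bias. An analyst who works from that sentence will compute RT(4,5) − RT(6,7), and every result will read correctly. The article shows no scoring syntax, so nobody can say that the data will be scored the wrong way. This stands, and it makes the harm conditional: inversion needs the formula coded literally *and* the interpretation applied unchanged. It does not remove the contradiction, because a programmer or later analyst is not told which sentence to follow.

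It is also fair to say that no test is affected and that the primary clinical outcomes (substance use, craving, relapse) do not use this score. Both points stand. Randomisation, sample size and data collection are untouched.

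A reader might infer that a moderator analysis will come out with the wrong sign. The article does not support this: *Clinical analysis* specifies no moderator model. What is at risk is how the hypothesis about baseline bias would be read.

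A reader might also infer that the single difference score is wrong because it merges engagement with disengagement and leaves out conditions 8 and 9 (2 conditions × 3 trials × 3 blocks = 18 of 72 trials). The article does not support that either. *Attentional bias modification training* assigns tracking time and switching time on the training task to the two processes, and brings in the visual search task to measure transfer: "enhanced ability to disengage from substance cues, we also included a visual search task to measure attentional bias". It mentions both aspects but does not commit to two search-task indices. A composite is a legitimate choice, and further indices may be set out in a fuller document that is not shown.

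**Conclusion.** The contradiction is real and follows from two adjacent sentences. The score as written has the opposite sign to its stated meaning for every participant whose two mean reaction times differ. This rests on no numerical assumption; the millisecond values above only illustrate it.

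The effect on the results depends on which sentence is followed:

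- Formula coded literally and read as stated: the direction of means, contrasts and the baseline-bias ranking reverses. A training that works would appear to have increased bias.
- Score computed as the interpretation implies: the results read correctly and the defect is confined to wording.

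In both cases the size of the test statistics and the p-values are the same. It would be too strong to say that the trial's analyses will be reversed, or that any planned test is invalid. The supported conclusion is that the article fixes a scoring rule for its manipulation check that disagrees with its own interpretation, and that this should be settled before the score is used.

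**What to change.** Make the two sentences agree, in either of two ways:

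1. Define the score as mean RT(conditions 4 and 5) minus mean RT(conditions 6 and 7), and keep the present interpretation; or
2. Keep the present formula and state that a negative score reflects bias towards substance-related cues.

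The first is simpler, because a larger score then means more bias, which suits both the manipulation check and the hypothesis about baseline bias. Whichever is chosen, check that the scoring syntax follows it, for instance by running the three rows of the table above through it.

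The cost is one line of text and one check of code. It needs no new data and changes no planned test.

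Separate indices using conditions 8 and 9 are optional. If wanted, RT(8,9) − RT(6,7) and RT(4,5) − RT(8,9) add up to RT(4,5) − RT(6,7), so they would split the first version exactly. They are not needed to correct this error.

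### The attentional bias score is defined with the opposite sign to its stated meaning: as written, a biased patient scores negative and a reduction in bias reads as an increase

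*Protocol article*

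**What the plan says.** The section on attentional bias assessment describes the Odd One Out task and, after Table 1, gives the scoring rule. The score is obtained by "subtracting the mean reaction time of trials with one neutral picture among 19 substance-relevant pictures (condition 4 and 5; see Table 1"), and that mean is taken away "from the mean reaction time of trials with one substance-relevant picture among 19 neutral pictures (condition 6 and 7").

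The next sentence interprets the result: "A positive score indicates that participants are faster in finding substance-relevant information within neutral information", as compared with finding a neutral picture in a substance-relevant array, "and thus reflect an attentional bias for substance-related cues".

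The score has several uses:

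- **Manipulation check.** It has this role in the sections on trial objective and on primary and secondary outcome measures. The objective section says an effect on substance use can be expected only if bias is modified.
- **Attribution.** The abstract says changes in bias will be used to judge whether changes in the primary outcomes can be attributed to bias modification.
- **First planned analysis.** In the clinical analysis section it is the dependent variable of a 4 × 2 repeated measures ANOVA.
- **Moderator.** The last hypothesis predicts that "participants who show a stronger attentional bias and higher rates of craving before starting the ABM training will benefit most from this intervention".

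**The concern.** The formula and its interpretation stand in adjacent sentences and point in opposite directions. The formula is positive when the patient is slower to find the substance picture. The interpretation says positive means faster.

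If the score is coded from the first sentence and read by the second, every conclusion about direction is reversed. A training that reduces bias would appear to increase it, and the manipulation check would seem to fail in the wrong direction. Ranking patients by baseline score would put those with the least bias at the end meant for those with the most, which would also reverse the moderator hypothesis. A benefit on substance use, or the lack of one, would then be given the wrong mechanism.

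The reversal would not show up as an odd test result. A significant group-by-time interaction looks equally convincing with either sign.

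**Working it through.** **Inputs, all from the section on attentional bias assessment**

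- A = mean reaction time in conditions 4 and 5: one neutral picture among 19 substance pictures.
- B = mean reaction time in conditions 6 and 7: one substance picture among 19 neutral pictures.
- Scale: reaction time, so a faster response is a smaller number.
- Stated direction: positive score = faster in conditions 6 and 7 = bias towards the substance.

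**Step 1. Are the condition labels swapped?** Table 1 lists condition 4 (alcohol version) as "19 alcohol 1 soft drink" and condition 6 as "19 soft drink 1 alcohol". Conditions 5 and 7 follow the same pattern with flowerpots, and the cannabis column matches. The labels agree with the formula text, so mislabelling does not explain the sign.

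**Step 2. The formula.** Subtracting A from B is B − A, so score = RT(6,7) − RT(4,5).

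**Step 3. The interpretation.** Faster in conditions 6 and 7 means RT(6,7) < RT(4,5). Then RT(6,7) − RT(4,5) < 0, so the patient described as having a positive score has a negative one. This holds for any reaction times; the two sentences are compatible only when the score is exactly zero.

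**Step 4. Illustration.** The document gives no reaction times, so these values are assumed and show only the sign.

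| Patient | RT(6,7), ms | RT(4,5), ms | As written: RT(6,7) − RT(4,5) | Swapped: RT(4,5) − RT(6,7) |
|---|---|---|---|---|
| Strong bias | 2,500 | 3,000 | −500 | +500 |
| Weaker bias after training | 2,800 | 3,000 | −200 | +200 |
| No bias | 3,000 | 3,000 | 0 | 0 |
| Slower to find the substance target | 3,200 | 3,000 | +200 | −200 |

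As written, reducing the bias moves the score from −500 to −200, a rise of −200 − (−500) = 300 ms. With the order swapped it moves from +500 to +200, a fall of 300 ms, as the interpretation requires.

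**Step 5. Effect on the planned test.** Multiplying every score by −1 changes the sign of all means and differences but not their variances. The ANOVA F statistics and their p-values are therefore the same. A check on two simulated groups of 64 showed this for a t-test: t = −3.297 became +3.297, with p = 0.00127 both times. Only the direction changes.

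**The case against.** The contradiction itself cannot be argued away, but there is a fair case that its consequences are limited.

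1. **The harm is conditional.** It arises only if the code follows the first sentence and the reader follows the second. The second sentence makes the intended direction plain, and a slip in wording is at least as plausible as a reversed score in the analysis. This stands: the document shows a contradictory definition, not a wrong result.
2. **The planned test does not change.** F and p are the same with either sign. This also stands, but a manipulation check has to establish direction, and the test statistic gives no warning that the direction is wrong.
3. **The score is not a clinical outcome.** Substance use, craving, relapse, costs and psychological complaints do not depend on it, and neither do eligibility, randomisation or sample size. This stands and limits the damage to the mechanism and moderator conclusions.
4. **It is reversible.** A sign change at any time corrects it without loss of data. That is true, provided somebody notices.
5. **The moderator consequence is inferred.** The clinical analysis section describes no moderator analysis, so how patients would be ranked by baseline bias is not stated. The consequence follows only if the score is used as defined.

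None of these points reconciles the two sentences. They bear on how serious the matter is, not on whether the text is wrong.

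**Conclusion.** The concern holds. The scoring rule and its interpretation contradict each other for every non-zero score. The discrepancy is a complete reversal of sign, whatever the reaction times. The conclusion rests only on the ordinary meaning of subtracting one quantity from another and on a faster response being a smaller reaction time.

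What is affected is the direction of the manipulation check, of the attribution of outcome change to bias change, and of the baseline-bias hypothesis. The size and significance of the bias analysis, and all clinical and economic outcome analyses, are unaffected. Whether any computed result would be wrong depends on the scoring code, which is not shown. A wrongly signed manipulation check would mislead and is hard to spot afterwards, so the text should be corrected before any bias result is computed.

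**What to change.** Reverse the order of subtraction: attentional bias score = mean RT(conditions 4 and 5) − mean RT(conditions 6 and 7). Leave the interpretation as it is. A positive score then means bias towards the substance, and a reduction in bias appears as a fall, which fits the way the hypotheses are worded.

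Keeping the present formula and stating that a negative score indicates bias would also be consistent. It is less convenient, because a reduction in bias would then appear as a rise in the score.

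Before any bias result is computed, run the scoring script on a constructed test patient who is faster in conditions 6 and 7 than in 4 and 5, and confirm that the score is positive. Carry the same definition into the analysis plan.

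The cost is one line of text and a short check of the script. Design, data collection and sample size do not change.

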#### Questionnaires

Participants’ general health state is assessed by means of the EuroQol-5D-3 L questionnaire [49]. Health care-related costs are evaluated with the Treatment Inventory of Costs in Psychiatric Patients questionnaire [50]. The Measurements in Addiction for Triage and Evaluation questionnaire [51] is a standard instrument in the Dutch addiction care and will be completed during the intake and at the end of the treatment through the therapists. During the 6 and 12 month follow-up measurements, the same questions will be asked online. For this study, the following parts of the MATE will be evaluated: substance use, the Obsessive-Compulsive Drinking Scale (OCDS5), and the Depression Anxiety Stress Scale (DASS).

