An important part of the study is the involvement of the therapists. In order to improve adherence, the researchers will train the therapists before the inclusion of participants starts. The training will consist of the following parts (1) general background knowledge about attentional bias and ABM, (2) design and important parts of the study, and (3) the role of the therapists. During the training all therapists will receive a protocol in which all important aspects are described. In the first session of TAU after patients are assigned to the study, therapists will identify the time of the day patients’ craving is strongest and will instruct the patient to complete the ABM task at this particular time of the day. Furthermore, during each following treatment session of TAU, the therapist will ask the participant whether he/she trains on a regular basis, and will engage in motivational counselling if this is not the case.

During the last week of TAU in addiction care, participants in the training conditions will receive the last training invitation by e-mail. After completion, they will be invited for the post-assessment. Participants in the TAU-only condition will also receive the invitation for the post-assessment in their last week of TAU. Finally, 6 and 12 months after the end of TAU, all participants will receive an invitation for the follow-up measurements by e-mail. In case a participant does not respond to these invitations, the researcher will remind the patient via the preferred way (phone, e-mail, text message or app). Throughout the length of the whole project, a sounding board group will meet four times to monitor the process of the study. The group will include a researcher, a therapist, and a member of the client council of each addiction care centre, and an implementation professional.

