#### Other measurements

During the baseline assessment, sociodemographic information will be collected, such as gender, relationship, level of education, and work. Furthermore, details of the patients’ own clinical history of addiction as well as of their family will be asked. Next, participants who are assigned to one of the training conditions will be asked about their expectations of the intervention. Before and after each training session, participants will rate their intensity of craving on a visual analogue scale (VAS), varying from 0 (no craving at all) to 100 (extreme craving). With this, possible direct effects of the intervention on subjective craving can be examined. Furthermore, at the end of the baseline assessment, all participants are asked to fill in a short questionnaire about their computer/laptop use in their private life. This information might be helpful when investigating for whom this iABM intervention was effective. Last, after the first week of training and during the post-assessment, participants, who are assigned to one of the training conditions, will be asked to fill in an evaluation questionnaire, in which they can give their opinion about the intervention and are asked to indicate whether the intervention helped them. Information derived from these questionnaires can be used as indications for possible next steps towards implementation. For an overview of all questionnaires and tasks per time point, see Table 2.

**Table 2 Tab2:** Overview of measurement instruments per time point

Purpose	Measures	Baseline	Post-assessment	Follow-up
Attentional bias assessment	Odd one out task	X	X	X
Baseline measures	Demographics	X		
	History of addiction	X		
	Family history of addiction	X		
Primary outcome measures - clinical	MATE (substance use, craving)	X	X	X
	Clinical state (relapse)			X
Primary outcome measures - Societal/economical	TiC-P	X	X	X
	EQ-5D	X	X	X
Secondary outcome measures	MATE (depression, anxiety and stress)	X	X	X
	Computer use	X		
Others	Expectation-questionnaire	X^a^		
	Training evaluation		X^a^	

^a^only to be filled in by participants in one of the training conditions

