### Blinding

Since all assessments take place online, thus in the absence of the researchers, the outcome data are blinded. However, one researcher will be aware of the condition of the participants in order to support them appropriately when technical or personal problems appear. It is unlikely that this will entail problems of bias, as the researcher is not involved in any measurement and the motivational part of the study lies in the responsibility of the therapists. The therapists and participants will be blinded for the two training conditions. Therefore, the iABM intervention and the placebo condition were designed such that the use of the same task stimuli would be possible, making both conditions look very similar. Furthermore, it is unlikely that participants will tell their therapists much about the content of the training, but more about whether they train regularly or whether they like or dislike the training. This will help to keep the therapists blinded. Furthermore, the therapists will be instructed not to do any ‘research’ about what might be the ‘real’ intervention. Participants will be asked to indicate their expectation about their condition in the post-assessment.

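### The end-of-treatment substance use, craving and DASS values are collected through therapists who can tell who is TAU-only, so the claim that all assessments are online and the outcome data blinded does not hold at that time point

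*Protocol article*

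**What the plan says.** Blinding section: "Since all assessments take place online, thus in the absence of the researchers, the outcome data are blinded". The same section limits the masking of people: "The therapists and participants will be blinded for the two training conditions".

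Questionnaires section: the MATE "will be completed during the intake and at the end of the treatment through the therapists". For later visits, "During the 6 and 12 month follow-up measurements, the same questions will be asked online". The parts of the MATE used are substance use, the craving scale and the DASS.

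Table 2 (under Other measurements) lists MATE substance use and craving as primary clinical outcomes, and MATE depression, anxiety and stress as secondary. All are marked at baseline, post-assessment and follow-up. Relapse is marked at follow-up only.

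Participants and procedure: therapists tell the patient at what time of day to do the training task, and in each later session "the therapist will ask the participant whether he/she trains on a regular basis, and will engage in motivational counselling" where needed.

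Clinical analysis: the post value is one of four time points in the repeated measures ANOVA of iABM against the two control conditions combined. Randomization: 50% iABM, 25% placebo, 25% TAU-only.

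**The concern.** The blinding claim is argued from one premise, that every assessment is online. For the first post-randomisation measurement of two primary outcomes, the Questionnaires section contradicts that premise. The person through whom the form is completed is the treating therapist, who has spent the treatment period encouraging some patients to train and has had no such task with others.

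The protocol supplies the test by which this fails. It considers the unblinded researcher harmless because that researcher takes no measurements and leaves motivation to the therapists. The therapist does both.

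At stake is a reported or recorded difference at the end of treatment that reflects knowledge of who had a training rather than an effect on use or craving. The trial report would also describe these outcomes as blinded when the protocol's own procedures say otherwise.

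**Working it through.** **Is the value collected blind?**

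1. The instrument for substance use, craving and DASS is the MATE (Table 2).
2. At the end of treatment it is completed through the therapists. At 6 and 12 months it is online (Questionnaires).
3. Therapists are blind to active versus placebo training (Blinding). They set the training time and ask about training only where there is a training (Participants and procedure). They can therefore separate trained from TAU-only patients, but not iABM from placebo.
4. The post value enters the ANOVA against pooled controls (Clinical analysis). TAU-only makes up 25/(25 + 25) = one half of those controls (Randomization).

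By contrast:

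| Contrast at end of treatment | Collected blind to condition by the therapist? |
|---|---|
| iABM v placebo | Yes, as planned |
| iABM v TAU-only | No |
| iABM v pooled control | No, for half of the control arm |

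**Sample size, reproduced first.** Assume that a medium effect means d = 0.5 and that the test is two-sided. A t-test at 5% with 80% power then needs 63.8, so 64 per arm. Inflating for 40% dropout gives 128/0.6 = 213.3, against the stated 213. The figure reproduces and this point does not change it.

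**Possible size of the bias.** The documents give none, so b is an assumption: the shift in SD units between trained and TAU-only patients that arises from knowledge of training status. Placebo patients share the trained patients' shift because the therapist cannot tell them apart. The spurious pooled difference is therefore b/2. With 64 per arm its standard error is √(2/64) = 0.177 SD. With no true effect, a two-sided 5% t-test at post rejects as follows:

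| b (SD) | Pooled shift b/2 (SD) | Rejection rate |
|---|---|---|
| 0.1 | 0.05 | 5.9% |
| 0.2 | 0.10 | 8.7% |
| 0.3 | 0.15 | 13.4% |
| 0.5 | 0.25 | 28.9% |

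In a direct iABM versus TAU-only comparison the full b applies.

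**In the planned ANOVA.** Put the shift at post only, with b = 0.3 and equal correlation ρ between the four times (assumed). For group × time the noncentrality is (64/2) × 0.15² × (3/4)/(1 − ρ) = 0.54/(1 − ρ), with 3 and 378 degrees of freedom. This is 0.77 at ρ = 0.3 and 1.80 at ρ = 0.7, and the rejection rates are 9.9% and 17.5%. For the group main effect, which averages over four times, the rate is about 6%.

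**The case against.** The best case on the other side has several parts.

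- **The phrase may mean less than it seems to.** Completion through the therapists could be no more than handing over a self-report form. That would weaken rater influence. It would not make the assessment online, and it would leave the form in the hands of someone who knows training status.
- **Part of the correction is already there.** The Blinding section does limit masking to the two training conditions. But it still concludes, without qualification, that the outcome data are blinded.
- **Patients know they are TAU-only anyway.** This stands. It is inherent in a TAU-only arm, and online collection removes only the therapist's part.

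A reader might also infer more than the documents support:

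- **That the change from therapist to online collection biases the treatment effect.** All arms change together, so a common mode shift falls on the time main effect. Bias in group × time would need a mode effect that differs by arm, and nothing in the protocol points to one.
- **That about 20% of post values will be missing.** The 20% under Sample size is dropout from regular addiction treatment, not a figure for missing MATE forms. The Withdrawal section still invites those who stop training to later assessments, and multiple imputation is planned. How the MATE is obtained after early exit from TAU is not stated.
- **That the intake MATE is compromised too.** Patients first hear of the study at intake or the first session and consent afterwards, so an intake value appears to precede allocation.

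**Conclusion.** The contradiction stands. At the end of treatment, substance use, craving and DASS are not collected blind for iABM versus pooled control or for iABM versus TAU-only, and the sentence claiming blinded outcome data is wrong for them. Relapse, both online follow-ups and the iABM versus placebo comparison are not touched by therapist collection, so the documents do not support a reading that the whole trial has lost its blinding.

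The size is unknown. Under the assumed range of 0.1 to 0.5 SD, the pooled post contrast moves by 0.05 to 0.25 SD, and the false-positive rate of a simple post comparison is about 6% to 29% (13% at 0.3 SD). These rates assume d = 0.5 planning, 64 analysed per arm, a two-sided test, and a shift shared by placebo and iABM patients. They illustrate how sensitive the contrast is and do not predict its bias. That therapists know TAU-only status is inferred from their duties and not stated, but the inference is firm.

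**What to change.** 1. Add the MATE substance-use, craving and DASS items, in the online form already used at 6 and 12 months, to the online post-assessment that every participant is invited to. Use these as the trial's post values. The therapist-completed MATE at end of treatment remains a clinical record.
2. Send that post-assessment to participants who leave TAU early as well, so that the value does not depend on a last session.
3. Keep the intake MATE as baseline. An online baseline copy is optional and should be used only if completed before allocation is disclosed. The online baseline follows registration and contains an expectation questionnaire for the training conditions only. Consent may also arrive as late as the third TAU session. Moving baseline there could replace a pre-allocation value with one taken after TAU has begun and allocation is known.
4. Reword the Blinding section: therapists and participants are blind only for iABM versus placebo, and comparisons involving TAU-only are open-label with self-reported outcomes.

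The cost is a few minutes of extra online questions and a wording change. The downside is that post is then collected in a different mode from the intake baseline, but equally in all arms.
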